### Case status

*WTC-AHR* will be defined as having a positive methacholine (PC_200_ < 16), or a positive bronchodilator response (by ATS/ERS guidelines with improvement of FEV_1_ by 12% and at least 200 mL) at least once post-9/11 [73, 74] and/or EMR diagnosis. *GERD* will be defined as: biopsy-proven erosive esophagitis LA grade C or D; stricture or Barrett’s esophagus on endoscopy; and/or esophageal acid exposure time > 6% on a pH or pH impedance study. GERD will also be defined on EMR diagnosis and/or PPIs, H_2_ blockers, antacid, or surface agent use [75]. *BE*, as a subset of GERD, will have any of the following additional inclusion criteria: biopsy-proven columnar epithelium lining ≥ 1 cm of the distal esophagus with intestinal metaplasia characterized with goblet cells on histology; diagnosis on EMR, Tables 2 and 3 [75]. The recruited participants will be consented prior to any research activity and measurement visit via REDCap software or in person.

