### Power analysis

A sample size of 40 cases for each group of GERD, AHR, AHR/GERD overlap, BE, and non-GERD/non-AHR Controls (all will be subsets of AIM 1 *N =* 898 randomly selected cohort) achieves 80% power to detect difference as small as 0.78 SD with two-sample t-test at 0.01 significance level to account for multiple comparisons. This will allow us to achieve 80% power and significance of 0.05, based on prior studies with salivary pepsin test (personal communication with [name] of Peptest), Fig. 2.

*Statistical Analysis* SPSS 28 (IBM) will facilitate database management and statistics. Continuous variables expressed as mean, standard deviation (SD) if normally distributed, and as median, inter-quartile range (IQR) if skewed. Two-sample t-test and ANOVA will compare continuous data. Count and proportions will summarize categorical data and Pearson- χ^2^ will compare categorical data. Multivariate binary logistic regression will estimate biomarker-disease relationship for case status as a binary outcome while adjusting for confounding. Cox proportional hazards model will evaluate the effects of biomarkers, smoking, and exposure on the hazard of developing WTC-GERD or BE over time. The maximum potential effectiveness of a biomarker will be calculated by Youden Index [100]. Goodness of fit, using the Hosmer–Lemeshow test. Survival curves compared by Log-rank test. Pearson χ^2^-test will compare SABA and LABA usage between GERD, AHR, AHR/GERD overlap, BE, and non-GERD or AHR controls. Significance will be assessed by *p <* 0.05 for all statistical tests. Graphs will be created using Prism (v.10, GraphPad Software).

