### Model building

We have previously identified key biomarkers using a machine learning approach [10, 28–30]. We have further refined this analysis pipeline and will utilize this methodology to identify AHR, GERD, AHR/GERD overlap, and BE biomarkers**.** Specifically, we will utilize random forests (RF) of the filtered, normalized biomarkers. Models assessed via a modified hamming distance between variable importance rankings of models with identical hyper-parameters. A refined profile of the top 5% of important biomarkers by MDA will be included in a gradient-boosted tree model (xgboost package, R-Project) to build a classifier of AHR, GERD, AHR/GERD overlap, and BE. A random hyperparameter space search determined a final model that maximized AUC_ROC_.

We will also use linear mixed-effects models will be used to assess the temporal trend of biomarkers with time adjusting for confounders. The longitudinal biomarkers processes will be associated to risk of developing WTC-GERD/BE using the joint modeling technique [101]. The joint-modeling approach has become the primary method for analysis of longitudinal biomarker process and time-to-event outcome, and multiple R packages are available to implement the models. We will also consider a single index longitudinal model which enables us to reduce the dimensionality of multiple biomarkers and to evaluate joint effects of multiple biomarkers together to identify key risk factors. The single-index model incorporates longitudinal data to calculate hazard of each parameter as well as personalized dynamic risk for prognostication. Specifically, this will allow us to use a patient’s data from a single clinical exam to identify risk of GERD, AHR, overlap, or BE. Furthermore, this will allow the identification of false negatives and undertreated cases in the entire FDNY cohort.

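### The pooled GERD/BE event in the joint model, and in the Cox model if its wording means one event, is GERD onset by definition, so Barrett's has no hazard of its own there

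*Protocol article*

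**What the plan says.** All places are in the Protocol article.

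- **Cox model** (Statistical Analysis paragraph under Power analysis): effects of biomarkers, smoking and exposure are to be evaluated "on the hazard of developing WTC-GERD or BE over time".
- **Joint model** (Model building): "The longitudinal biomarkers processes will be associated to risk of developing WTC-GERD/BE using the joint modeling technique".
- **Definitions** (Case status): BE, "as a subset of GERD, will have any of the following additional inclusion criteria". One route to a GERD diagnosis is "stricture or Barrett’s esophagus on endoscopy".
- **Recruited cohort** (Study population): the overlap group is formed from GERD/BE together with AHR, so GERD/BE is used there as one category. BE is also recruited as a group of its own.
- **Single-index model** (Model building): this is something the authors will consider. It is meant "to calculate hazard of each parameter as well as personalized dynamic risk for prognostication", and the next sentence claims it will use a patient's "data from a single clinical exam to identify risk of GERD, AHR, overlap, or BE". No event is named for it.
- **Case-status models**: a gradient-boosted tree is planned "to build a classifier of AHR, GERD, AHR/GERD overlap, and BE", and logistic regression is planned for case status as a binary outcome.

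**The concern.** The named time-to-event outcome does not match the risks that the hazard models are said to deliver. Four conditions are listed for prognosis, but the only event written down pools two of them, and one of those two is contained in the other. When one condition is a subset of another, a first-of-either endpoint carries no information about the narrower one.

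Barrett's is in the study title and is the premalignant condition that motivates the work. The Limitations section expects to show that biomarkers can predict GERD, BE or both. If the pooled event is used, a marker of the step from GERD to BE goes unseen, and a marker of GERD onset could be reported as a marker of GERD/BE although BE played no part in the estimate.

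**Working it through.** **1. The plan's own figure.** The only reproducible design figure is 40 per group for a difference of 0.78 SD, two-sample t-test, significance level 0.01 (taken as two-sided) and 80% power. By the normal approximation, n = 2(2.576 + 0.842)² / 0.78² = 38.4, so 39 per group. With the noncentral t distribution, 40 per group gives 79.9% power and a detectable difference of 0.781 SD. The figure reproduces. It does not bear on the hazard models, for which the article states no event count and no hazard ratio.

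**2. The pooled event equals GERD onset.** Let T_G be the time a man first meets the GERD definition and T_B the time he first meets the BE definition. Since every BE case is a GERD case, T_G ≤ T_B. Hence min(T_G, T_B) = T_G for every man. This follows from Case status alone and needs no assumed rate.

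**3. Which hazards are named.**

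| Outcome | Cox model | Joint model | Single-index model | Case-status models |
|---|---|---|---|---|
| GERD | yes | yes | event not named | yes |
| BE alone | only if the wording means two outcomes | no | event not named | yes |
| AHR | no | no | event not named | yes |
| Overlap | no | no | event not named | yes |

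**4. Illustration of what pooling hides.** From the article: 837 men in the sub-cohort, and 44% with GERD by 2005 (Background, for rescue and recovery workers). Assumed, because the article gives none: a constant GERD hazard with 2005 taken as year 4, so −ln(1 − 0.44)/4 = 0.145 per year; 16 years of follow-up; progression to BE at 0.005 or 0.02 per year after GERD; and a standardised marker. These assumptions imply GERD in 1 − 0.56⁴ = 90% of the men, about 755, by year 16. Thirty simulated cohorts were run per scenario.

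Marker with no effect on GERD onset (ranges are over the two progression rates):

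| True progression HR per SD | Pooled GERD/BE | BE as its own event | BE timed from GERD onset |
|---|---|---|---|
| 1.5 | 1.00 to 1.01 | 1.50 to 1.51 | 1.51 to 1.52 |
| 2.0 | 1.00 to 1.01 | 1.92 to 1.97 | 1.97 to 2.00 |
| 3.0 | 0.99 to 1.00 | 2.66 to 2.90 | 3.00 to 3.06 |

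The pooled and GERD-only hazard ratios were equal in every scenario, as step 2 requires.

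**5. When the pooled hazard ratio is not 1.**

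- *The marker also acts on GERD onset.* With an HR of 1.2 on onset the pooled HR is 1.19 to 1.21. With 1.5 it is 1.48 to 1.51. It tracks the GERD effect whatever the progression effect is.
- *Some men have BE at first diagnosis.* If a share s of first diagnoses is already BE and the marker acts only on that part, the pooled HR is roughly (1 − s) + s × HR. For HR = 2: s = 5% gives 0.95 + 0.10 = 1.05, and s = 20% gives 0.80 + 0.40 = 1.20.

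**The case against.** **Risk of AHR, overlap and BE is not estimated at all.** A reader might infer this, but the documents do not support it. The classifier keeps all four phenotypes apart, and logistic regression addresses case status. The sentence promising the four risks follows the single-index model, which is only under consideration and has no named event, so it could be fitted to each condition. The reference to one clinical exam, and the aim of finding false negatives and undertreated cases, are at least partly about present disease. For AHR and overlap the gap is therefore close to detail that an article may leave to the full protocol. What remains is that the claim is framed as hazard and dynamic risk for prognosis, while no time-to-event outcome is named for AHR, overlap or BE alone.

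**The Cox sentence may mean two outcomes.** This is a fair reading. BE has its own criteria and its own recruited group, and the Limitations section speaks of GERD and/or BE. On this reading BE has its own hazard in the Cox model. The joint model's GERD/BE is written as one event and is not rescued, although a slash is thin evidence of intent.

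**A marker of Barrett's will show a hazard ratio of about 1.** This too might be inferred, but only under conditions. It needs a marker without effect on GERD onset and few men with BE at first diagnosis. The article gives no rates for progression and does not say what the markers act on.

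**Definitions may sit elsewhere.** The endpoints table and the study design figure are not visible here, and no analysis plan is at hand. Either might separate the outcomes. The visible text nevertheless states the pooled event and the definition that collapses it.

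**Conclusion.** The concern holds in this form: read as one event, GERD/BE is identical to GERD onset under the article's own definitions. The joint model as written therefore gives no BE risk, and the Cox model gives one only if its wording means two outcomes. That conclusion rests on the definitions and needs no assumption about rates.

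The size is illustrative. For a marker acting only on progression, with a true hazard ratio of 1.5 to 3 per SD, the pooled model shows about 1.0. For a true ratio of 2 it shows about 1.05 to 1.20 if 5 to 20% of first diagnoses are already BE. If the marker also acts on GERD onset, the pooled model reports that effect and says nothing about BE. Progression rates, follow-up and hazard ratios are assumed throughout. For AHR and overlap the finding is narrower: the prognostic claim goes beyond the time-to-event outcomes named.

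**What to change.** - **Cox and joint models.** Replace the pooled event with two outcomes reported separately: GERD onset, and BE onset. Time BE from GERD onset, or treat GERD and BE as successive states in a multi-state model. State how men whose first qualifying diagnosis is already BE are handled, since they have no time at risk after GERD; a direct transition to BE is one way.
- **Single-index model.** Name its event or events. Either fit AHR and overlap as their own events where onset dates are available in the EMR, or limit the prognostic claim in Model building to the outcomes actually modelled.
- **Case-status models.** No change is needed. The text should say that they address current status.

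The cost is wording and a few additional models. BE will have fewer events and so wider intervals. In the illustration without an effect on GERD onset, BE events averaged 44 to 192 against about 755 for GERD. As standard errors scale with 1/√events, intervals for the log hazard ratio would be about √(755/192) = 2 to √(755/44) = 4.1 times as wide. The change also relies on usable onset dates in the EMR: the article defines AHR as a positive test at least once after 9/11 and/or an EMR diagnosis, and does not say that onset dates are held.

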**Methods:**

Our observational case-cohort study will leverage the longitudinally phenotyped Fire Department of New York (FDNY)-WTC exposed cohort to identify *Biomarkers of Airway Disease, Barrett’s and Underdiagnosed Reflux Noninvasively (BAD-BURN)*. Our study population consists of *n =* 4,192 individuals from which we have randomly selected a sub-cohort control group (*n =* 837). We will then recruit subgroups of *i.* AHR only *ii.* GERD only *iii.* BE *iv.* GERD/BE and AHR overlap or *v.* No GERD or AHR, from the sub-cohort control group. We will then phenotype and examine non-invasive biomarkers of these subgroups to identify under-diagnosis and/or treatment efficacy. The findings may further contribute to the development of future biologically plausible therapies, ultimately enhance patient care and quality of life.

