### Microbiome of the gut/lung axis

Asthma susceptibility is influenced by the gut microbiome [106–111]. Noninvasive collection sites that can approximate the pulmonary environment are of key interest. Studies have failed to show that the microbiomes of induced sputum were similar to the lung [112, 113]. Noninvasively collected oropharyngeal and nasopharyngeal swabs in conjunction could approximate the lung microbiome [114]. Research has revealed that the esophageal microbiome undergoes alteration in individuals with GERD, BE, and other motility disorders [115, 116]. Although these findings highlight the potential role of the microbiome studies in the diagnosis and therapeutic approaches for aerodigestive disease, further studies are needed and will be one of the key readouts planned in our study.

*EBC* analysis holds great promise in addressing unmet medical needs by expanding the portfolio of noninvasive assays for the multiple coexisting pathological mechanisms underlying respiratory disorders and GERD. Compounds identified in EBC include histamine, adenosine, ammonia, hydrogen peroxide, isoprostanes, leukotrienes, nitrogen oxides (NOx), peptides, cytokines, protons and various ions [85]. Histamine plays a vital role in digestion but elevated levels can contribute to the development of GERD [117, 118].

*Salivary pepsin* has been studied in several GERD biomarker studies [105]. Due to the overlap of various reflux symptoms with other GI pathologies, the diagnosis of GERD can be challenging. However, salivary pepsin test offers a simple and convenient way for detecting reflux through salivary sample collection, providing quick and non-invasive results. Compared to other diagnostic modalities, this approach is time-efficient and requires much less effort [119]. Moreover, pepsin measurements can identify pathologic reflux even in the absence of symptoms, and remain unaffected by the concurrent use of PPI. Several studies have demonstrated that pepsin detection in the sputum and/or saliva can be regarded as a sensitive, non-invasive method for the diagnosis of the proximal reflux of gastric contents, with a sensitivity ranged from 41.5% to 73% and high specificity of 86.2 to 98.2% [78, 79]. Despite these findings little is known about pepsin in the context of aerodigestive co-morbid disease.

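### Models fitted to the clinical GERD label cannot identify that label's false negatives, because undiagnosed participants have no independent reference test

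*Protocol article*

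**What the plan says.** The abstract's Methods paragraph makes under-diagnosis a purpose of the study: the team will "phenotype and examine non-invasive biomarkers of these subgroups to identify under-diagnosis and/or treatment efficacy".

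The Case status section sets the GERD label. Objective findings (endoscopy, biopsy, acid exposure on a pH study) qualify, but so do routine records and medication: "GERD will also be defined on EMR diagnosis and/or PPIs, H_2_ blockers, antacid, or surface agent use".

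The models take these clinical groups as their outcome. Under Power analysis, "Multivariate binary logistic regression will estimate biomarker-disease relationship for case status as a binary outcome while adjusting for confounding". Under Model building, a boosted-tree model is used "to build a classifier of AHR, GERD, AHR/GERD overlap, and BE", and "A random hyperparameter space search determined a final model that maximized AUC_ROC". The same section adds joint models and, as an option to be considered, a single-index longitudinal model for the risk of these same conditions. It then concludes: "Furthermore, this will allow the identification of false negatives and undertreated cases in the entire FDNY cohort".

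The Limitations section foresees participants without a GERD history whose questionnaires or biomarkers point to GERD, and recommends that they see a gastroenterologist. It does not say that the result returns to the study data.

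**The concern.** A classifier fitted to a label learns to reproduce that label. When it calls a label-negative person positive, two explanations are open: the label missed a true case, or the model is wrong. Separating them needs information on true disease that comes from neither the label nor the model.

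The text from Measurement visit through the questionnaires lists blood, saliva, spirometry, exhaled nitric oxide, breath condensate, swabs, questionnaires and cognitive tests. It lists no endoscopy and no oesophageal pH study. The Background itself calls GERD diagnosis partly subjective and poorly sensitive. Silent cases may therefore also sit among the training negatives, where the model is taught to call them negative.

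Underdiagnosed reflux is in the study title. If flagged participants are reported as false negatives, ordinary misclassification would be presented as missed disease, and the sentence extends that reading to the whole cohort.

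**Working it through.** **The plan's own figure.** The article gives no figure for under-diagnosis. Its sample-size statement (40 per group, 0.78 SD, 1% level, 80% power) reproduces: a noncentral t calculation, taken as two-sided, gives 79.9%. It concerns differences between group means and does not bear on this point.

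**The identity.** Among label-negative participants, let u be the share who truly have GERD, and let Se and Sp be the model's sensitivity and specificity against true disease. The flagged share is

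f = (1 − Sp) + u × (Se + Sp − 1).

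The study observes f. Without a reference test, u, Se and Sp are all unknown, so f does not determine u.

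**Inputs for an illustration.**
- Label-negative recruits: AHR only (40) plus neither condition (40), from Study population, gives 80.
- Accuracy: the Discussion quotes salivary pepsin "with a sensitivity ranged from 41.5% to 73% and high specificity of 86.2 to 98.2" per cent. It stands in for the final model, whose accuracy is not known.
- Assumption: u = 0.

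**Flags when no one is under-diagnosed.**

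| Specificity | Expected flags among 80 | Chance of at least one |
|---|---|---|
| 98.2% | 80 × 0.018 = 1.4 | 1 − 0.982^80 = 77% |
| 86.2% | 80 × 0.138 = 11.0 | 1 − 0.862^80 > 99.9% |

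For the 40 men with neither condition alone, the chance is 1 − 0.982^40 = 52% to 1 − 0.862^40 = 99.7%.

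**What one flagged share can mean.** Solving the identity for u gives the Rogan-Gladen form, u = (f + Sp − 1) / (Se + Sp − 1). With f = 13.8%:
- Sp 86.2%: u = (0.138 + 0.862 − 1) / (Se + 0.862 − 1) = 0 for either quoted Se.
- Sp 98.2%, Se 73%: u = 0.120 / 0.712 = 17%.
- Sp 98.2%, Se 41.5%: u = 0.120 / 0.397 = 30%.

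The same observation fits no under-diagnosis, or nearly one in three.

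**A check that does not use pepsin.** A simulation took one normally distributed score and correct labels, fitted a Youden cut on 40 cases and 40 controls, and applied it to 40 new controls (2,000 runs). Mean flags were 15 at AUC 0.71 (the 0.78 SD difference), 7.9 at AUC 0.90 and 2.1 at AUC 0.99. At least one control was flagged in 99.95%, 99.6% and 80.7% of runs. None was a missed case, by construction.

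**The case against.** The other side has real points. The article never writes the rule that a positive model with a negative label makes a missed case. The sentence follows a single-index model that is only to be considered, which yields hazards and dynamic risks and not a yes/no call. No under-diagnosis rate is listed under Outcomes. Pepsin has a fixed external cut-off and is not trained on the label, so its specificity is a loose proxy. Discordant participants are anticipated and referred. A fuller protocol or SAP could hold thresholds, validation and a misclassification correction, and the article's Tables 1 to 3 are not shown.

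Much of this stands as a limit on size: the numbers illustrate and do not predict. It does not rescue the sentence. The claim is made outright, and every model described takes the clinical conditions as its outcome. A risk score must still be compared with the label before anyone can be called a false negative. Pepsin and symptom scores come from outside the label, but they are not a reference standard. Referral addresses the participant's care but supplies no confirmation that the analysis is said to use.

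**Conclusion.** The concern holds as a limit on what can be concluded. With the design as described, missed disease and model error cannot be separated among label-negative participants, so the sentence claims more than the study can show. In the illustration, 1.4 to 11.0 of 80 men are flagged with no under-diagnosis at all, and one flagged share of 13.8% fits 0% as well as 17% to 30%. These figures assume that pepsin accuracy stands in for the model and that errors are independent between men.

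A reader might infer three stronger things, which the documents do not support:
- *The flagged share measures only classifier error.* The identity shows that it rises with u whenever Se + Sp exceeds 1. It is a mixture.
- *False findings arise in almost every run.* At the top quoted specificity the chance of any flag is 77% among 80 men and 52% among 40. For a very large cohort it is near 100% with almost any imperfect test, so it says nothing particular about this plan.
- *A definite number of false flags in the whole cohort can be computed.* Saliva is described only for the recruited participants, and the 44% GERD figure in the Background describes WTC rescue and recovery workers in 2005, not this cohort.

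**What to change.** 1. In Model building, replace the claim to identify false negatives and undertreated cases with identification of biomarker-positive participants without a diagnosis. Align the abstract's under-diagnosis wording. Reserve *false negative* for participants with objective confirmation in the record.
2. Report the flagged share beside the share expected from the model's out-of-sample false-positive rate, and draw no conclusion on under-diagnosis unless that share is exceeded. The rate must not be taken against the clinical label itself: among label-negatives the two shares would then agree by definition. Take it from participants with negative objective tests or, if they are too few, show an assumed range.
3. If enough participants have endoscopy or pH results in the EMR, add the Rogan-Gladen estimate as a sensitivity analysis. State that tested patients are selected and that the reference is itself imperfect. The article does not say how many have such results, so this should not be the main estimate.

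The cost is a wording change, one added comparison and a weaker statement on under-diagnosis. No new procedure is needed.
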